**5e. Strategies for recruitment and retention**

**Aim 1:** *Adaptation of PRO-ACT by stakeholders:* We will leverage the expertise and professional networks the study team has within the mental health and adolescent HIV care domains to purposively select stakeholders who will be involved in the workshop adapting the PRO-ACT training for healthcare providers. We will purposively select up to 40 stakeholders who will include:

1. Representatives from the Ministry of Health Departments of Mental Health and Adolescent Health

2. Representatives from the County health departments, specifically those overseeing the adolescent HIV program and mental health programs

3. Representatives from the National AIDS and STI Control Program (NASCOP) overseeing the adolescent HIV program

4. Representatives of HIV care implementation partners (non-governmental organizations supporting the adolescent HIV program)

5. HIV and mental health researchers and academics from various universities, NGOs and teaching hospitals in Kenya and the University of Washington

6. Representatives from regional HIV Technical working Groups

7. Frontline healthcare providers working in HIV clinics

8. Youth living with HIV nominated by the youth-led advocacy groups

9. Caregivers of adolescents and youth living with HIV nominated by advocacy groups

10. Adolescent and youth mental health advocates in Kenya

The stakeholders will be reached in-person or via phone call or email to be informed about the study. They will then receive a formal invitation to the workshop. We will provide them periodic updates of the study to maintain their engagement in the project. They will receive reimbursement for the time used in study activities.

**Aim 1:** *Provider training:* Providers in intervention clinics who will receive the PRO-ACT training will be purposively selected by the HIV clinic head (~6 per clinic). They will be providers of different cadres (clinicians, nurses, counselors and peer educators) working directly with youth. Their contact information will be collected by the study staff from the clinic head, and they will provide consent to participate in the training and subsequent study procedures.

**Aim 2:** *Supervision and optimization of PRO-ACT delivery in intervention sites:* Each trained provider (up to 6 per intervention site) will screen youth receiving care at their clinic ages 16-24 years for depression, anxiety or trauma symptoms during their routine clinic or antiretroviral treatment refill visits. Each provider will be allocated at least one AYHIV with mild to moderate symptoms of psychological distress. The AYHIV will be consented and enrolled into the study to receive the PRO-ACT intervention, where over a 3-6 month period, they will attend sessions depending on their availability. They will be reminded of their scheduled sessions via a phone call or text message, a week and a day before the session. The sessions will be supervised by a PRO-ACT trainer (psychologist), with a debriefing between the supervisor and provider also done after the session. The providers will hold bi-weekly meetings to optimize the intervention. The providers will receive reimbursement for the time they perform study activities, while the AYHIV will be reimbursed for the cost to get to the clinics and time in study activities.

**Aim 2 and 3:** *Healthcare providers* trained in intervention sites will implement PRO-ACT; and complete surveys and interviews. Additionally, providers in both intervention and control sites will be recruited to participate in surveys and interviews to assess the implementation of the intervention and determinants of implementation. They will receive reimbursement for their time completing surveys and participating in interviews.

*Adolescents and youth with HIV* will be recruited by study staff in the intervention and control clinics after the provider training and intervention optimization is complete during their routine clinic or refill visits. The clinic staff will introduce the study staff to the youth during triage who will then describe the aims of the study. Those interested in participating will undergo screening by the study staff before or after the clinic visit. All adolescents and youth ages 16-24 years in the participating clinics will be screened for psychological distress (symptoms for depression, anxiety or trauma) using recommended tools by the study staff. Approximately 300 participants in intervention clinics and 300 in control clinics with symptoms of psychological distress will be referred to the clinic staff for appropriate interventions (PRO-ACT in the intervention sites, standard of care in the control sites) and follow up. Phone contact information of the youth receiving the intervention and their caregivers or other trusted individuals that they identify will be collected by the study team. We will also collect and update their physical location information for tracking purposes where required. The adolescents will receive phone call reminders of their clinic visits and we will leverage the clinic mechanisms for home tracing/visits in the event that they are unreachable by phone. Youth that participate in the intervention will complete surveys and a sample will be invited for qualitative interviews to assess implementation outcomes and provide cost information. They will be reimbursed for transport to attend the sessions and for the time used in study activities.

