**5d. Site/Participant exclusion criteria**

A facility may be excluded if there are barriers to conducting provider training or data collection/ abstraction. Individuals will be excluded if any study procedure would put them at an increased risk or if their compliance with study procedures is not possible. Adolescents below 16 years will be excluded since we expect that majority of them will require additional interventions targeting caregivers since they have not achieved independence in care, and have not been fully disclosed to their HIV status. This younger age group therefore requires a separate study with an intervention adapted to their needs.

| **Table 3: Populations involved in the study** | | | |
| --- | --- | --- | --- |
| **Aim** | **Design** | **Approach/strategy and data source** | **Participant numbers and inclusion characteristics** |
| AIM 1: Adapt and optimize the training on PRO-ACT and the intervention delivery | Cross-sectional | Stakeholder workshop | 40 stakeholders including policymakers, frontline providers, researchers, representatives of adolescents and youth with HIV (AYHIV) and other community members |
|  |  | Continuous quality improvement (CQI) of PRO-ACT delivery in 15 public HIV clinics selected for the cluster randomized trial as intervention sites | Approximately 120 providers ≥18 years old at 15 intervention clinics (up to 6 per site trained on the PRO-ACT intervention); and up to 6 AYHIV age 16-24 years per site. |
| AIM 2: Test effectiveness of the PRO-ACT intervention | Cluster randomized trial | 30 public HIV clinics each with at least 100 AYHIV | AYHIV age 16-24 years attending public HIV clinics. We expect ~2400 AYHIV will be screened and ~300 AYHIV with mild to moderate psychological distress will be followed-up in each arm, with the ~300 in the intervention clinics receiving the intervention |
|  |  | Survey assessing provider satisfaction with training | Up to 90 trained providers ≥18 years old at 15 intervention clinics (up to 6 per site) |
|  |  | Surveys | All AYHIV (~2400) ages 16-24 years in the 30 participating clinics will be screened using mental health assessment tools in a survey.  The ~300 AYHIV followed up in each arm will complete follow up surveys every 3 months |
|  |  | Routine clinic data | Clinic notes and viral load results will be abstracted from the charts and electronic medical records repositories for all AYHIV (~2400) ages 16-24 years in the 30 clinics |

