| AIM 2: Assess implementation and service outcomes and determinants of implementation |  | FGDs with providers | Up to 30 with 7-10 participants each from the intervention and control facilities ≥18 years old |
|  |  | IDIs with providers | Up to 6 IDIs with providers from each participating clinic |
|  |  | FGDs with AYHIV | Up to 30 with 7-10 participants 16-24 years each from intervention facilities |
|  |  | Competence assessments using the ENACT tool | Up to 90 trained providers ≥18 years old at the 15 intervention clinics |
|  |  | Fidelity assessments using a standardized checklist | Up to 90 trained providers ≥18 years old at the 15 intervention clinics |
|  |  | Quantitative surveys with AYHIV | ~600 AYHIV involved in the intervention |
|  |  | Routine clinic records for AYHIV | All AYHIV in the 30 clinics ages 16-24 years |
|  |  | Checklist in the patient chart | All AYHIV (~2400) AYHIV 16-24 years in the study sites |
|  |  | Quantitative survey with facility/HIV clinic heads | 30 facility/ HIV clinic heads from selected study sites |
|  |  | Quantitative surveys with providers | Up to 6 providers from each of the 30 selected study sites |
| Aim 3: Conduct an economic evaluation of the intervention |  | Time in motion studies for provider time | Providers in the 30 adolescent HIV clinics |
|  |  | Interviews with program officers with information on program administration | 30 program officers in the HIV clinics |
|  |  | Quantitative surveys with AYHIV | ~600 AYHIV involved in the intervention |

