**7e. Cluster Randomized Controlled Trial (RCT)**

All AYHIV attending the 30 participating clinics will be screened for depressive, anxiety and trauma symptoms by study staff during their routine clinic visits. *This will differ from the required PHQ-9 or -2 mental health screening by clinic staff during routine visits.*^85^ Study staff will classify AYHIV based on severity of symptoms (mild/moderate/severe) as described above.

For inclusion in the cluster randomized trial, AYHIV eligibility criteria include: symptoms of depression, anxiety or trauma, age 16-24 years, willingness to consent to study procedures.

*Intervention sites:* AYHIV with mild/moderate symptoms of depression/anxiety/trauma will be offered PRO-ACT; all sessions will be delivered by trained providers in the clinic on an agreed schedule within 6 months. The study staff will conduct 3-monthly assessments for participating AYHIV via phone or in-person, and 6-monthly medical record abstraction for viral load results.

*Control sites:* AYHIV with mild/moderate symptoms will be offered referral (by the study staff) to available psychosocial support within the clinic as per standard of care practices. They will complete 3-monthly assessments (administered by study staff) and 6-montlhy medical record abstraction for viral load results.

*The standard of care:* Kenyan guidelines for the provision of HIV services and adolescent friendly services recommend screening of all AYHIV during their routine clinic visits using the PHQ2/9. While psychotherapy is recommended for those with elevated depressive symptoms, the provision of this service is dependent on whether there is a provider in the facility with training to offer it. ART adherence counseling is however offered by nurse counselors, which includes aspects of motivational interviewing and problem solving techniques. HIV clinic-mental health specialist interfaces though recommended are not developed in majority of clinics.^109,120^

In both intervention and control sites, AYHIV who have severe symptoms or who have suicidal ideation will be referred for specialized care. In Nairobi Youth will be referred to KNH youth Clinic, Mathari hospital CHild and Adolescent clinic or Ngaira Youth clinic- Nairobi County. In Kisumu and Homa Bay youth will be referred to the nearest level 4 or 5 county hospital with psychiatric services.

Table 1 above summarizes the study procedures to assess effectiveness of PRO-ACT

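### As written, contact collection, and the reminders and tracing that depend on it, cover only youth receiving the intervention; the protocol should state that they apply identically in both arms

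*Protocol*

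**What the plan says.** Section 5e is the only place where the protocol describes how trial participants will be kept in follow-up. It first introduces about 300 youth in intervention clinics and 300 in control clinics, who "will be referred to the clinic staff for appropriate interventions (PRO-ACT in the intervention sites, standard of care in the control sites) and follow up". The next sentence is the one at issue: "Phone contact information of the youth receiving the intervention and their caregivers or other trusted individuals that they identify will be collected by the study". It continues: "We will also collect and update their physical location information for tracking purposes where required". Then: "The adolescents will receive phone call reminders of their clinic visits and we will leverage the clinic mechanisms for home tracing/visits", the home tracing being for those who cannot be reached by telephone.

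Section 7e describes follow-up arm by arm. Under intervention sites it says: "The study staff will conduct 3-monthly assessments for participating AYHIV via phone or in-person". Under control sites it has study staff administer 3-monthly assessments but gives no mode.

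Other sections make clear that both arms are followed. Table 3 (section 5d) has about 300 youth per arm completing surveys every 3 months, and the table of staff roles in section 7f assigns follow-up surveys in both intervention and control clinics to study staff.

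**The concern.** The protocol gives 5e's limiting phrase a specific meaning elsewhere. Table 3 separates the youth followed in each arm from those treated, "with the ~300 in the intervention clinics receiving the intervention", and section 5f contrasts fifteen clinics that get standard of care with fifteen that get the intervention. On that meaning, control youth have no contact details on file and so no basis for reminder calls or tracing.

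Two comparisons would be exposed.

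- **Symptom scores (primary).** They are measured five times over 12 months. If control youth are harder to find, scores are missing unequally by arm. Section 13h names mental health problems as a major driver of loss to follow-up, so those lost may well be the more symptomatic.
- **Viral suppression (the only secondary effectiveness outcome).** It is taken from clinic records. The reminders are for clinic visits, so they could affect attendance, refills and whether a viral load is drawn. Given in one arm only, they would be a co-intervention that no analysis could separate from PRO-ACT.

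Section 5g states that clinics and study team cannot be masked, so masking would not keep staff effort equal.

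**Working it through.** **1. Who is covered, item by item**

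- *Phone contacts (5e):* youth receiving the intervention. Control youth are not named.
- *Location (5e):* a possessive that refers back to the same youth.
- *Clinic-visit reminders and home tracing (5e):* the adolescents, with no arm stated. Calls need a number, and tracing is triggered by failure to reach someone by phone, so in practice both depend on the contacts just described.
- *Assessment every 3 months (Table 3, 7e, the roles table in 7f):* both arms.
- *Assessment by phone or in person (7e):* stated for intervention sites, not stated for control sites.
- *Contact collection, reminders or tracing expressly for control youth:* found nowhere.

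The session reminders described earlier in 5e belong to the pre-trial optimization phase and do not bear on this point.

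**2. The plan's own figure**

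The power table in section 12a can be reproduced, which fixes the scale for what follows. Inputs from 12a and 5f: 15 clinics per arm, m participants per site, ICC, R² of 0.05 (individual) and 0.01 (site), alpha 0.05 taken as two-sided.

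se² = 2 × [ICC × (1 − 0.01) + (1 − ICC) × (1 − 0.05)/m] / 15

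For m = 20, ICC = 0.03, d = 0.3:

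se² = 2 × [0.03 × 0.99 + 0.97 × 0.95/20] / 15 = 2 × [0.0297 + 0.0461] / 15 = 0.0101, so se = 0.1005 and d/se = 2.98.

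A noncentral t with 28 df gives power 0.821, against 0.82 in the table. All 18 cells reproduce within 0.02. The table assumes no loss to follow-up, and the wording question does not change it.

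**3. Illustration: loss of precision (assumed retention)**

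Same scenario, with m reduced separately by arm:

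- 100% in both arms: power 0.82
- 90% in both arms: 0.80
- 90% intervention, 80% control: 0.78
- 90% intervention, 70% control: 0.76
- 90% intervention, 60% control: 0.74

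Precision suffers modestly. Bias is the larger worry.

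**4. Illustration: bias in the symptom comparison (assumed values)**

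Let L_C and L_I be the proportions lost in control and intervention. Let δ be how much worse, in SD, those lost score than those retained, taken as equal in both arms. The retained control mean is too good by L_C × δ and the retained intervention mean by L_I × δ. The treatment difference therefore moves towards no effect by

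bias = (L_C − L_I) × δ

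- Gap 10 points, δ = 0.2: 0.10 × 0.2 = 0.02 SD
- Gap 10 points, δ = 0.5: 0.10 × 0.5 = 0.05 SD
- Gap 20 points, δ = 0.2 to 0.5: 0.04 to 0.10 SD
- Gap 30 points, δ = 0.2: 0.30 × 0.2 = 0.06 SD
- Gap 30 points, δ = 0.5: 0.30 × 0.5 = 0.15 SD

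Against the powered effects this is 0.02/0.2 = 10% to 0.15/0.2 = 75% of d = 0.2, and 0.02/0.4 = 5% to 0.15/0.4 = 37.5% of d = 0.4.

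The direction is towards hiding a benefit. A one-arm prompt to attend clinic would more likely exaggerate a benefit on viral suppression. The documents give no figure from which to size that effect.

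**The case against.** The strongest reply is that this is loose drafting and that both arms were meant. Much of it stands.

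- The sentence just before the contact sentence calls PRO-ACT and standard of care alike appropriate interventions and sends both groups for follow-up.
- Later in the same paragraph: "Youth that participate in the intervention will complete surveys and a sample will be invited for qualitative interviews". Taken literally, only one arm would be surveyed, which Table 3, section 7e and the roles table in 7f contradict.
- Table 3 twice counts roughly "600 AYHIV involved in the intervention", which is both arms together.
- Section 11a names the 3-monthly instrument an intervention follow-up survey and gives it to everyone with mild to moderate symptoms enrolled in the trial.
- The study team must reach control youth every 3 months anyway, and home tracing uses existing clinic mechanisms. Section 7e does not exclude phone assessment in control sites; it is silent.
- The models in 12c include baseline symptom scores, which may absorb part of any selective loss.

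A reader might go further and infer that the protocol plans unequal retention, or that attendance will differ by arm. The documents do not support that. The reminder and tracing sentence names no arm, no section states a difference as intended, and no retention figure is given.

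The reply does not settle the matter. The operative phrase concerns receiving the intervention, which Table 3 and 5f use for the PRO-ACT arm. The same paragraph reimburses these youth for transport to sessions, and for the trial itself sessions are described only for PRO-ACT. No sentence extends the procedures to control youth, so a team working from the text could follow either reading.

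**Conclusion.** The point holds as an ambiguity with real consequences, not as a demonstrated design difference. Read literally, 5e collects contacts in one arm, the reminders and tracing depend on those contacts, and 7e states a phone mode for one arm only. A drafting slip is at least as likely as a planned difference, but nothing in the protocol corrects it.

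If the text is followed as written, unequal retention could hide a benefit on symptoms and one-arm prompting could exaggerate a benefit on viral suppression. The two act in opposite directions on different outcomes, so they do not offset each other.

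The size is unknown. The range of 0.02 to 0.15 SD rests wholly on assumed retention gaps of 10 to 30 points, an assumed difference of 0.2 to 0.5 SD between lost and retained youth that is the same in both arms, and no correction from baseline adjustment. It shows that the matter could be material; it does not estimate the bias.

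**What to change.** In section 5e, replace the phrase limiting contact collection to youth receiving the intervention with one naming all trial participants in both arms (about 600). State that contact and location collection, clinic-visit reminders and home tracing follow the same steps in both arms. In section 7e, give the same assessment modes for intervention and control sites. Any PRO-ACT session reminders may stay in the intervention arm as part of the intervention.

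Identical procedures are enough; there is no need to restrict reminders to study assessments.

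The cost is a few sentences of protocol text and some extra calls to control participants whom the study must already contact every 3 months. It is best settled before enrolment, because contacts never collected and follow-up already lost cannot be recovered in the analysis.

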**5f. Randomization procedures**

For the cluster randomized controlled trial, the 30 clinics will be randomized to intervention and control clinics. Clinics will be randomized using computer generated random numbers to either intervention or control status, using restricted randomization to balance for county. Randomization will be performed at UW by a biostatistician with access only to the clinic characteristics of interest. After randomization, the list of clinics and allocation arms will be given to the study team. Fifteen clinics will receive standard of care (screening and referral to available services) and 15 will receive the intervention (screening, PRO-ACT and referral to available services where applicable).

**5g. Masking procedures**

PRO-ACT will be administered at the clinic-level; therefore, it is not possible to blind participating clinics or study team members.

**5h. Participant Withdrawal**

Participants may withdraw from this study at any time. The Principal Investigator may also terminate a participant’s participation.

Reasons for Withdrawal

- Clinics may stop participation from the study if they face closure or major changes in HIV and mental health treatment policies or organizational structure that would negatively impact the conduct of the study.
- Providers may stop participation from the study if they face discomfort/ distress from the training or study procedure, or lack time to participate in the study procedures or if they face job termination or relocation from the study sites.
- Adolescents and youth with HIV may stop participation from the study if they face discomfort/ distress from the intervention, or lack time to participate in the study procedures, including completing surveys or participation in interviews.
- The Principal Investigator may terminate the continued participation of AYHIV or provider’s involvement in the study if they have a medical condition or are involved in a situation where continued participation in the study would not be in their best interest or if their behavior prevents the successful completion of study procedures.

Handling of participant withdrawals

- The study team will track and record the withdrawal of any clinic or participant during the study. The participants will be assured that their withdrawal from the study will not affect their employment or services received in the clinic. They will be thanked for their time in the study and not contacted further by the study team. Depending on the timing of the withdrawal, the Principal Investigator will make a decision on replacement of the clinic or participant.

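### Section 5h permits replacement of randomised clinics at the discretion of an unblinded investigator and does not separate stopping PRO-ACT from leaving follow-up

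*Protocol*

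**What the plan says.** Section 5h opens by allowing withdrawal at any time and adds: "The Principal Investigator may also terminate a participant’s participation". The grounds for this include a medical condition or situation in which continuing is not in the person's interest, "or if their behavior prevents the successful completion of study procedures". Among the reasons given for youth, they "may stop participation from the study if they face discomfort/ distress from the intervention"; lack of time for study procedures, surveys included, is another.

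On handling withdrawals, 5h says of those who leave: "They will be thanked for their time in the study and not contacted further by the study team". It then says: "Depending on the timing of the withdrawal, the Principal Investigator will make a decision on replacement of the clinic or participant".

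Three other sections bear on this.
- **5f:** the 30 clinics are allocated 15 to 15 by restricted randomisation balanced on county, and the list of arms then goes to the study team.
- **5g:** "it is not possible to blind participating clinics or study team members".
- **5e:** youth are recruited after provider training and optimisation are complete, so every withdrawal by a trial participant comes after clinic allocation. It also plans to collect "Phone contact information of the youth receiving the intervention and their caregivers or other trusted individuals".

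The primary outcomes (3a, Table 1) are PHQ-9, GAD-7 and CATS or PCL-5 scores from surveys at baseline and months 3, 6, 9 and 12. Viral load, the secondary outcome, comes from clinic records.

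**The concern.** There are two separate problems in 5h.

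**Replacement.** The decision is made case by case by someone who knows the arm, and nothing confines it to the period before randomisation. A clinic brought in later has no place in the restricted randomisation. The arms are also exposed differently: between allocation and enrolment only intervention clinics go through training and several months of supervised optimisation (7c, 7d), so they have more occasion to falter and be swapped. A substitution cannot be undone at the analysis stage.

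**Follow-up.** As written, a youth who stops PRO-ACT because it is distressing, or whose participation the investigator ends, can be handled as having left the study, with no further contact. The primary outcomes need contact, so those scores are lost. Control youth receive no PRO-ACT, so the distress reason bears mainly on the intervention arm. If those lost are doing worse than average, the remaining intervention youth look better than the arm really is. An analysis plan can define who is analysed, but it cannot recover surveys that staff were told not to conduct.

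**Working it through.** **1. The plan's own figure.** The power table in section 12a sets the scale. Inputs from 12a: 30 sites, 20 participants per site, ICC 0.03, d = 0.3, alpha 0.05 (taken as two-sided), R² 0.05 at individual level and 0.01 at site level.

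Var = 4 × [0.03 × 0.99 + 0.97 × 0.95 / 20] / 30 = 4 × 0.075775 / 30 = 0.010103, so SE = 0.1005.

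Noncentrality = 0.3 / 0.1005 = 2.98; with 28 df, power = 0.821. The table states 0.82. All 18 cells reproduce to within 0.005. The table makes no allowance for loss.

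**2. Uneven loss, true effect zero.** Assumptions not in the protocol: a fraction f of one arm goes unobserved, and those people would have scored k SD worse than their arm mean. The observed arm mean then shifts by f × k / (1 − f). The type I error uses the SE above.

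| f | k | Spurious effect (SD) | Type I error |
|---|---|---|---|
| 5% | 0.5 | 0.05 × 0.5 / 0.95 = 0.026 | 0.057 |
| 5% | 1.0 | 0.05 × 1.0 / 0.95 = 0.053 | 0.080 |
| 10% | 0.5 | 0.10 × 0.5 / 0.90 = 0.056 | 0.083 |
| 10% | 1.0 | 0.10 × 1.0 / 0.90 = 0.111 | 0.187 |

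The trial is powered for effects of 0.2 to 0.4 SD.

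**3. Uneven loss, true effect 0.30 SD.** Simulation under assumed inputs: 300 per arm, five visits with correlation 0.6, loss in the intervention arm only and more likely with a worse month-3 score (log odds 0.8 per SD), 1,000 trials per setting.

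| Loss | Month-12 completers only | Using the month-3 score |
|---|---|---|
| 15% | 0.324 | 0.297 |
| 25% | 0.348 | 0.304 |

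The completers-only estimate is 8% and 16% too large (0.324 / 0.30 and 0.348 / 0.30). A model that uses the month-3 score removes the bias, because here loss depends only on a score that was observed. It would not do so if loss depended on distress arising after the last survey.

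**4. One swapped clinic.** One clinic is 1/15, or 7%, of an arm. If the substitute differs by q between-clinic SDs, the arm mean moves by q × √ICC / 15. At ICC 0.03, √0.03 = 0.173, which gives 0.012 SD for q = 1 and 0.023 SD for q = 2. Over the ICC range in 12a (0.01 to 0.05), the shift is 0.007 to 0.030 SD.

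**The case against.** The strongest reply is that 5h says nothing about the analysis. It does not say that withdrawn or replaced units are dropped, and the analysis set may be defined in a statistical analysis plan that is not shown. This stands. A reader might infer that the protocol itself breaks the intention-to-treat comparison; the text supports only that it permits a break.

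A reader might also infer that only intervention youth can leave. The documents do not support that: 5h lets anyone withdraw at any time, and lack of time for surveys applies in both arms. Nor does 5h state that ending sessions ends follow-up. Sections 7e and 11a schedule 3-monthly surveys for trial youth whatever their session attendance. What stands is that 5h does not draw the distinction, and its no-contact rule has no exception.

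The 5e sentence on contact details could be read as tracing in one arm only. It is probably loose wording: Table 3 describes all of the roughly 600 trial youth as involved in the intervention, and 5e puts no arm limit on reminders and home tracing.

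On size, the 8 to 16% overstatement needs loss in one arm only and a complete-case analysis. Section 12c fixes neither, and the bias disappears once the month-3 score is used.

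Replacing a youth within an allocated clinic is further recruitment, and harms mainly if the original is dropped. The listed grounds for clinic withdrawal are closure or major policy or organisational change, not results. Ending contact is proper where a person withdraws consent to all follow-up.

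**Conclusion.** The concern holds in a limited form. Section 5h gives an unblinded investigator discretion to replace a randomised clinic with no criteria and no cut-off, and nothing else in the protocol restricts it. It also leaves a route by which youth who only stop PRO-ACT, or whose participation the investigator ends, are lost to the surveys that carry the primary outcomes, with one reason for leaving tied mainly to the intervention arm.

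The size cannot be fixed from the protocol. Under the assumptions shown, uneven loss of 5 to 10% gives a spurious 0.03 to 0.11 SD, and a single swapped clinic at ICC 0.03 gives 0.012 to 0.023 SD. The first range can matter for a trial powered at 0.2 to 0.4 SD. The second is small, but it is a departure from randomisation that analysis cannot repair. Neither is a forecast of what will happen. The case for changing the text is that the safeguard is cheap now and unavailable once a clinic has been swapped or surveys have been missed.

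**What to change.** 1. In 5h, replace the replacement sentence with a rule that no clinic is replaced after randomisation, and that all randomised clinics and enrolled youth stay in the analysis in their allocated arm. Any further recruitment in an allocated clinic adds to, and does not substitute for, those who withdrew.
2. In 5h, separate stopping sessions, or investigator-ended participation in the intervention, from withdrawal of consent to follow-up. For the former, continue the 3-monthly surveys and chart abstraction unless the participant refuses. Keep the no-contact rule for those who withdraw consent to follow-up.
3. In 5e, state that contact collection, reminders and tracing apply to trial youth in both arms.

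The cost is protocol and consent wording, slightly more follow-up effort, and acceptance that a lost clinic is not made up. For scale, at d = 0.3, ICC 0.03 and 20 per site, power falls from 0.82 with 30 clinics to 0.79 with 28 and 0.76 with 26.
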